#### EOC staff

In the main trial site, the use of live streaming has been approved at organisation level and thereby staff are not individually consented to use live streaming but instead will be given the opportunity to opt out of trial shifts. They will otherwise be required to follow organisational protocols if they are working on a trial shift. In the observational substudy, HEMS dispatchers and critical care APPs will consent on an individual basis to being observed using live streaming. The researcher will contact staff to invite them to participate in an interview about the use of live streaming in their organisation. The local PI at both EOCs participating in the staff survey will share the staff survey link with all eligible staff pre-trial. All staff who enter their email address to complete the post-trial survey will be emailed a link to the survey post-trial. Those who participate in the staff survey at the main trial site will be invited to partake in an interview about their views and experiences of live streaming; selected to include different types of staff, for example, age, gender and experience.

### Assignment of intervention

Working shifts are randomised 1:1 to intervention (GoodSAM) or standard ambulance care using a minimisation algorithm to ensure balance between weekday/weekend (Mon–Thurs vs Fri–Sun) and daytime/night-time shifts (06:00 to 18:00 vs 18:00 to 06:00).

A small number of shifts in the final observation week will be used to test the feasibility of individual call randomisation using a pre-prepared randomisation list. All randomisations will be undertaken by a statistician at Surrey Clincial Trials Unit to ensure the allocation is independent of the research team.

### Data collection methods

#### Observations of EOC processes

An experienced researcher will observe EOC processes, decision making processes, fidelity to the protocol and impact of contextual variability (eg, time of day, weather) during the trial weeks in the main trial site (3–6 hours for 3 days in each observation week). In the observational substudy, a second experienced researcher will observe up to 24 shifts over a 3- month period. Observational data will be recorded using fieldnotes capturing both descriptive and conceptual observations/interpretations.

The observational and interview data collection and analysis will be underpinned by theories informing the proposed mechanisms of effect, for example, situational awareness (SA)^26^; decision making (DM)^27^; the implementation of a new technology (TAM)^28–30^ and Consolidated Framework for Implementation Research.^31^ Events will be observed in real time and the use of live streaming will be understood in the context of how the use of visual technology impacts on staff assessment of situations and action taken (SA and DM), as well as the factors influencing how people relate to the introduction of a new technology (TAM). Equally, in situations where live streaming is not used, theories of SA and DM will inform observations in context.

#### Decision making data and clinical data from trauma patients

During the trial weeks, the RPs will collect data live during incidents including the CAD number; information about decision making; the patients’ name, age and sex (if available); details of the trauma incident (eg, single/multiple casualties; general nature of incident, eg, road traffic collision/assault); dispatch decisions and the use of live streaming for example, quality of sound/picture. This information will be recorded on a piloted, study-specific proforma completed at the time of the incident. Further details about EMS dispatch (including speed to appropriate dispatch) and time stamped data for each incident will be accessed by RPs after the incident.

Following consent to access medical records (process described in recruitment section), the RPs will extract relevant information from patients’ medical records about the injuries sustained and the treatments received (up to 3 months post-incident). Using the expert panel algorithms, the RPs will rate the appropriateness of dispatch. A random 10% sample of incidents from intervention and control calls will be independently reviewed by the expert panel using the same data, to assess reliability.

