### Intervention and randomisation

999 calls in the main trial site during the six observation weeks (up to 42 days; 84 shifts) will be randomised 1:1 to working shift intervention or standard care. Control shifts will follow standard care ambulance dispatch protocol with a 999 caller using a telephone (voice only) and the call taker using NHS Pathways ambulance dispatch tool.

In the intervention arm, a live streaming technology called GoodSAM Instant-on-Scene^23^ will be tested. The technology allows a 999 caller to stream live video footage from the scene of an incident to the EOC. 999 calls allocated to intervention will initially follow the standard NHS Pathways dispatch protocol until ambulance dispatch prioritisation has been determined. EMS will be dispatched as normal, without delay. The call handler in the EOC will then transfer the caller to the HEMS dispatcher or critical care paramedic (CCP) and live streaming will be activated. EMS resource allocation may be adjusted following this.

If at any point the dispatcher feels they do not want to view the scene (eg, due to psychological impact of viewing the scene) or it is not safe to continue, the 999 caller will be thanked for their help and the call will be ended. The dispatchers will be provided with training and guides outlining the trial processes to ensure adherence to intervention and study protocols.

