### Outcomes

#### Primary outcomes

The primary outcome is the decision regarding the feasibility of undertaking a definitive RCT based primarily on meeting the specified progression criteria (see table 3).

**Table 3 T3:** Progression criteria from feasibility RCT to future RCT

GREEN; proceed to definitive study—GO	AMBER; consider protocol amendments to improve criteria	RED; do not proceed to main trial—STOP
≥70% of callers with smartphones agreeing and able to activate live streaming	≥50% of callers with smartphones agreeing and able to activate live streaming	<50% of callers with smartphones agreeing and able to activate live streaming
≥50% of requests to activate live streaming resulting in footage being viewed	≥30% but <50% of requests to activate live streaming resulting in footage being viewed	<30% of requests to activate live streaming resulting in footage being viewed
Air Ambulance (HEMS) stand-down rate reducing by ≥10% and/or change in dispatch decision as a result of live streamed footage confirmed as being appropriate in ≥10% cases	Air Ambulance stand-down rate reducing by ≥5% and/or change in dispatch decision as a result of live streamed footage confirmed as being appropriate in ≥5% cases	No change in Air Ambulance stand-down rate and/or change in dispatch decision as a result of live streamed footage
Rates of psychological harm (based on the survey measures) not significantly greater in 999 callers using live streaming compared with those not; and no significant difference in change to psychological harm over time in staff (CCPs, HEMS dispatchers, research paramedics) compared with change in staff in a comparison EOC not using live streaming/streamed from scene footage	–	Evidence of significantly greater harm in either 999 callers or EOC staff using live streaming compared with EOC not using live streaming.

CCP, critical care paramedic; EOC, emergency operations centre; HEMS, helicopter emergency medical services; RCT, randomised controlled trial.

In addition to the quantitative progression criteria described in table 3, the research team will consider qualitative data collected as part of this study (eg, interviews, observations and free text questions in surveys) when reviewing progression to a definitive RCT.

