### Sample size

We estimate there will be approximately 250 trauma incidents (including 300 patients) over the six observation weeks (125 allocated to intervention), which will allow for an estimate of true event rate within precision of ±0.75 events per day; and allow estimation of speed to appropriate response with an SE of <5%. These sample size estimations are based on convenience sampling over the six defined trial observation weeks. We estimate there will be approximately 350 lay public 999 callers (250 from the main trial site and 100 from the observational substudy) and up to 202 EOC staff (86 from the main trial site, 30 from the observational substudy and 86 from the third EOC).

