### Recruitment: identification and consent

#### Trauma patients

Trauma patients will be identified by research paramedics (RPs), using the eligibility criteria. RPs will observe all trial shifts. For eligible calls in the main trial site, the computer-aided dispatch (CAD) number(s) relating to the incident will be recorded by the RP as the identifier to share with the conveying hospital to approach for consent. Informed consent will be sought from either the patient, their consultee or the patient’s parent or guardian (either in the hospital before discharge or via telephone, email or post) in all hospital trusts included in the trial (trauma units and major trauma centres covered by the EOC). RPs may consent patients in person with assistance from the hospital to identify the patient(s). Approval has been granted by the Confidentiality Advisory Group (Section 251 application) to access medical records for casualties who die before consent can be sought (and where there is not a power of attorney in place for that individual). National data opt-out status will be checked for all deceased patients.

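### The 10% panel check of dispatch appropriateness is not aimed at the changed decisions that progression row 3 counts, and would hold about one of them at the GREEN minimum; no masking is stated for raters or panel.

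*Protocol article*

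**What the plan says.** In the Protocol article, under Trauma patients (recruitment), "RPs will observe all trial shifts". Under Decision making data and clinical data from trauma patients, the same staff group completes a proforma during each incident that covers dispatch decisions and the use of live streaming. It later extracts the medical records, and then: "Using the expert panel algorithms, the RPs will rate the appropriateness of dispatch". The check on those ratings is: "A random 10% sample of incidents from intervention and control calls will be independently reviewed by the expert panel using the same data". Its stated purpose is to assess reliability.

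Under Secondary outcomes, the algorithms are to be agreed by experts before the trial starts and take the form of a binary decision tree. Appropriateness means that the resource sent was needed for treatment or transport. Medical records are used where consent is given.

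Under Primary outcomes, Table 3 row 3 is met at GREEN by a reduction of at least 10% in the air ambulance stand-down rate and/or by changed decisions due to footage "confirmed as being appropriate in ≥10% cases". The AMBER thresholds are 5%. The table has four rows, and qualitative data are also weighed.

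**The concern.** The raters belong to the group that watched the shifts and recorded whether video was used, so the arm is likely to be known when appropriateness is judged. Allocation is kept independent of the research team (Assignment of intervention), but no comparable protection is stated for this assessment.

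The panel check is the one stated safeguard on the ratings once they are made. It draws incidents at random from both arms, whereas row 3 counts a small subset of one arm. A sample that represents all incidents will contain very few from that subset.

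Two things are at stake. The first is whether the changed decisions counted in row 3 can be called confirmed on anything beyond the RP's own rating. The second is that the same ratings define the speed of appropriate dispatch, whose estimates by arm are meant to inform the definitive trial's sample size. A rating tendency that differed by arm would carry forward.

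**Working it through.** **Inputs.** From Sample size: "approximately 250 trauma incidents (including 300 patients) over the six observation weeks (125 allocated to intervention". From Intervention and randomisation: "six observation weeks (up to 42 days; 84 shifts) will be randomised 1:1". From Table 3: thresholds of 10% (GREEN) and 5% (AMBER). From the data collection section: a 10% review sample. The article does not give the number of changed decisions, the consent rate or the meaning of *cases* in row 3, so these are varied below.

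**The plan's own figures.** The event rate is 250/42 = 5.95 per day. The Poisson 95% half-width is 1.96 × √(5.95/42) = 0.74, which agrees with "estimate of true event rate within precision of ±0.75 events per day". The standard error below 5% fits a proportion of 0.5 with n = 125: √(0.25/125) = 4.5%. The figures of 250 and 125 are therefore a sound base.

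**Size of the check.** 10% of 250 is 25 incidents, of which about 12.5 are intervention.

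**Changed decisions needed, if *cases* means all 125 intervention incidents.** GREEN: 0.10 × 125 = 12.5, so at least 13 (13/125 = 10.4%). AMBER: 0.05 × 125 = 6.25, so at least 7. Thirteen is the fewest changes that can give GREEN, because every one must then be rated appropriate.

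**How many fall in the check.** With k changed decisions the expected number sampled is 0.10 × k. The chance of none is hypergeometric: C(250−k, 25)/C(250, 25) for 25 drawn from all 250, or C(125−k, 13)/C(125, 13) for 13 drawn within the intervention arm.

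| Changed decisions k | Expected in check | P(none), 25 of 250 | P(none), 13 of 125 | P(at most one), 25 of 250 / 13 of 125 |
|---|---|---|---|---|
| 7 (AMBER minimum) | 0.7 | 47% | 45% | 85% / 84% |
| 13 (GREEN minimum) | 1.3 | 25% | 22% | 62% / 60% |
| 25 | 2.5 | 6% | – | – |

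Drawing the sample overall or within arm makes little difference (the expectation for k = 13 is 1.3 or 1.35).

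**Other denominators.** If *cases* means incidents with footage viewed, assumed to be 50% to 30% of 125 (about 62 to 38), GREEN needs 7 to 4 changes and the check holds about 0.7 to 0.4. If only consented incidents can be rated, with consent assumed at 25% to 75%, the GREEN threshold expectation of 0.10 × 12.5 = 1.25 becomes 0.3 to 0.9.

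**What the check can show.** If all 25 sampled incidents agreed, the exact 95% lower bound for agreement would be 0.025^(1/25) = 86%. For a single sampled change that agreed, the bound would be 2.5%. With kappa 0.6 and chance agreement 0.5 (both assumed), observed agreement is 0.8, the standard error is √(0.8 × 0.2/(25 × 0.5²)) = 0.16, and the 95% half-width is 1.96 × 0.16 = 0.31.

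**The case against.** The strongest defence is the decision tree. It is agreed by experts before the trial, is binary, and rests on whether the resource sent was needed. That limits the rater's discretion, and the point stands. It does not mask the rater, who still extracts the facts that enter the tree.

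A second defence is that the sample is meant to assess reliability, and about 25 incidents from both arms do test whether RPs apply the tree as the panel would. That also stands, with the imprecision shown above. It would be wrong to call the check worthless.

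A reader might infer that a handful of ratings settles progression, since a fall from 13 to 6 confirmed cases moves 10.4% to 4.8%, from GREEN to below AMBER. The documents do not support this. Row 3 can also be met through the stand-down rate, it is one of four rows, and qualitative data are considered. The fall would also require 7 of 13 ratings (54%) to be overturned, and nothing in the article suggests such an error rate.

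A reader might also infer that each rating is made by the RP who watched that incident, that the panel sees the arm, or that RPs deliver the intervention. The article says none of these. It does not link rater to shift. It does not list the fields the panel receives, although use of the same data suggests that streaming use is among them. It gives activation of the stream to the HEMS dispatcher or critical care paramedic. What remains is that the RP proforma would show streaming use to any RP who rates from it.

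The full protocol may hold more detail on masking. But the article itself fixes who rates, on what data, and the size and random nature of the check.

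**Conclusion.** The point holds in a limited form. The check can give a rough estimate of overall agreement, but it cannot support the claim that the changed decisions in row 3 were confirmed as appropriate. About 1.3 of them would be reviewed at the GREEN minimum, about 0.7 at the AMBER minimum, and about 2.5 if 25 decisions changed.

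These figures assume 250 incidents, 125 of them intervention, and all 125 as the denominator. Narrower denominators or incomplete consent lower them; more frequent changes raise them. That the arm is known to the raters is inferred from the RPs' observing and recording roles and the absence of stated masking. The weakness affects one limb of one criterion and the appropriateness estimates passed to the next trial. It does not invalidate the feasibility decision, but it is cheap to correct and should be corrected.

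**What to change.** Have the existing expert panel review every incident with a changed dispatch decision, mixed with the planned random intervention and control incidents. The panel should judge the appropriateness of the final dispatch from extracts with arm, live-stream use and the RP rating removed, and its rating should be the one that counts for row 3. Keep the overall agreement estimate on the random 10% alone, because the enlarged set over-represents changed decisions.

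Whether a change resulted from the footage cannot be judged from masked extracts. Take that separately from the RP proforma.

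Cost: at the GREEN minimum, 13 − 1.3, or about a dozen extra panel reviews; with 25 changes, 25 − 2.5, or about 22 to 23. The stripped extracts must also be prepared. Having all other incidents rated by an RP who was not on that shift is not proposed, because the article does not give RP numbers and this might need more staff.

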#### 999 callers

999 callers in the main trial site will be invited to complete surveys via Qualtrics online survey software^32^ 6–8 weeks post incident to assess psychological harm and semistructured interviews regarding experiences and acceptability of the use of live streaming. The questionnaire will include demographic questions, The Impact of Events Scale—Revised,^24^ The General Health Questionnaire-12 item version^25^ and questions about acceptability and experience of live streaming.

In the inner-city observational substudy, 999 callers will be invited to complete surveys via Qualtrics^32^ up to 1 week after the incident. The questionnaire will include a demographic questionnaire and questions about their experiences of using live streaming during their recent 999 call for example, ease of use, usefulness. Those who take part in the questionnaire will be invited to participate in an interview regarding experiences and acceptability of using live streaming.

999 callers at both sites who participate in the survey will be offered the choice of a £10 shopping voucher or £10 donation to the local air ambulance charity. A second voucher or donation will be offered to those who complete an interview.

#### EOC staff survey and interviews

Before the trial starts, EOC staff at the main trial site and staff well-being substudy will be emailed by the local principal investigator (PI) including the PIS, consent form and a link to the online survey via Qualtrics.^32^ The survey will include a demographic questionnaire, The Impact of Events Scale—Revised,^24^ The General Health Questionnaire-12 item version^25^ and questions about live streaming. Those who complete both pre-trial and post-trial questionnaires will be entered into a prize draw for one of five £50 retail vouchers (five available at each site). In the main trial site, approximately 12–18 staff will be invited to participate in an interview and will be paid overtime rates for their participation. Staff in the observational substudy who take part in an interview will be compensated for their time with a £45 Amazon voucher. The different methods for reimbursing time have been requested by the respective organisations.

### Data management

A detailed data management plan has been produced outlining the processes for completion, transfer and storage of study data in line with the Ambulance Trust and University policies, the requirements of the Sponsor and General Data Protection Regulation (GDPR). The data management plan will be shared with all those responsible for data collection on the trial and will form the basis of a Data Protection Impact Assessment and data processing agreements between the parties.

### Statistical methods and data analysis

#### Quantitative analysis

A full statistical analysis plan (SAP) will be reviewed by key members of the research team and approved by the steering committee before analysis is undertaken.

As this is a feasibility study, statistical analysis will focus on providing estimates and confidence intervals of key rates such as the number of eligible calls per day, uptake of video intervention and timing and appropriateness of dispatch to inform a subsequent RCT. Outcome measure will be summarised by arm and estimates reported with confidence intervals to inform future sample size calculations.

The SAP will outline any expected exploratory analysis of outcomes that may be useful to inform a subsequent RCT including any signal of potential efficacy, but it is noted that the study is not powered for this and so any interpretation would be limited to the direction and magnitude of any effect. Missing data (including outcome data) will be summarised, but all observed data will be included in any analysis according to the randomised allocation following the intention-to-treat principle.

#### Qualitative analysis

The process evaluation will include analysis of live streaming usage data; observations of EOC processes and interviews with staff and 999 callers. All interviews in the main trial site and observational substudy will be digitally recorded and transcribed verbatim. Once the transcripts have been checked for accuracy, recordings will be deleted. Transcripts will be analysed thematically using the Framework Method.^33^ Data will be analysed concurrent to its collection where possible and will inform the topic guides for interviews.

#### Health economic analysis

A health economic analysis will be undertaken from NHS and societal perspectives to inform the design of a full economic evaluation within the future RCT. The primary purpose of the health economic analysis is to assess the feasibility of gathering data on the resource implications, costs and effects of the dispatch decisions under standard care and when adjusted for the live streaming intervention.

### Data monitoring

A data monitoring committee was not required as this study is a feasibility study and there is no interim analysis.

### Harms

The study teams and participating staff at EOCs will inform the Chief Investigator and/or Sponsor as soon as they are aware of a possible serious breach that could impact the safety, or physical or mental integrity of subjects/participants in the study, so that the Sponsor can fulfil its regulatory and oversight requirements. Other deviations from the protocol will be recorded and dealt with appropriately.

